### 12.3 Secondary Variables - Efficacy

#### Haemodynamics

- SAP, DAP, MAP, HR, CVP, CI, SV, SVR
- cumulative dose of norepinephrine (mcg/h)
- intrathoracic blood volume index (ITBVI) and extravascular lung water index (EVLWI), (PICCO)

Measurements see 12.2

#### Ventilatory support

- Time on ventilator (measured from intubation in hours)
- Requirements of postoperative ventilatory support (PCV, CPAP)

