
\* if not otherwise mentioned measurements of secondary variables on ICU will be performed until fit-for-discharge from ICU criteria are fulfilled or until postoperative day 5 (including), whatever occurs first.

Efficacy:

- Haemodynamics
  - SAP, DAP, MAP, HR, CVP, CI, SV, SVR
  - cumulative dose of norepinephrine (mcg/h)
  - intrathoracic blood volume index (ITBVI) and extravascular lung water index (EVLWI), (PICCO)
- Time on ventilator (*measured from intubation in hours; the need of reintubation will be documented*)
- Requirements of postoperative ventilatory support (PCV, CPAP)
- Nursing Delirium Screening scale (NuDesc) – *measurement three times daily on ICU\**
- gastrointestinal parameters - (*measurement daily from post-op day +1 until fulfilment or until end of study, whatever occurs first*)
  - time until bowel movements (on auscultation)
  - time until full oral nutrition
  - time to first flatus
  - time to first defecation
  - intraabdominal pressure *measured baseline (after induction of anaesthesia), at the end of surgery (still in operating theatre before extubation), 6 hours after surgery, 1st post-operative day in the morning*
- SOFA, SAPS II, APACHE II Scores – *surveyed once daily on ICU\**
- length of stay in ICU/IMCU (fulfillment of ICU/IMCU release criteria according to the Aldrete Score, Aldrete 1995) *surveyed on admission to ICU, 1st postoperative day in the morning, at time of discharge from ICU*
- time until criteria for “fit for discharge from hospital” are fulfilled (hospitalization release criteria according to Marshall et al., 1999, Marshall and Chung, 1997) *surveyed once daily on ICU respectively surgical ward (if fit-for-discharge criteria are not fulfilled within the 5th postoperative day it will be controlled until fulfillment or until end of study, whatever occurs first)*
- Complication rate - surgical complications such as re-do surgery (e. g. anastomotic insufficiency or bowel leakage), disturbed wound-healing or medical complications which delay time to fully oral nutrition – *documentation at the study end*
- combined outcome parameter of prolonged length of stay (based on mean length of stay according to the German Diagnosis Related Group System D-DRG) or death (determination will be when DRG-data are available, i. e. after study end)
- Health Related Quality of Life (HRQoL) according to the EQ-5D questionnaire – *measurement baseline and 3 months after surgery*

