### Intraabdominal pressure

Measurements will be

- baseline (after induction of anaesthesia)
- at the end of surgery (still in operating theatre, directly before extubation)
- 6 hours after end of surgery
- 1st post-operative day in the morning

Technique:

Intraabdominal pressure will be obtained by measuring the intravesical pressure with the patient in a supine position. The bladder will be flushed via the transurethral catheter via a three-way stopcock using 25 mLs of sterile saline. The bladder will be emptied until air reaches three-way stopcock in order to exclude air bubbles in the system and to guarantee patency. As measurement volume 25 mLs sterile saline will be instilled. The manometer/pressure transducer will be connected to the transurethral catheter/connection to bladder via a three-way stopcock. Zero-reference will be at the midaxillary axis (same reference as CVP). Confirmation of correct measurement will be done by control of respiratory variation and the endexpiratory value will be noted.

In the awake patient (measurement at 6 hours after end of surgery and on 1st postoperative day in the morning) pain assessment will be made prior measurement of intraabdominal pressure using visual analogue scale (VAS).

Categories for pain assessment will be

|          |                      |
|----------|----------------------|
| VAS 0    | no pain              |
| VAS 1-3  | mild pain            |
| VAS 4-6  | medium/moderate pain |
| VAS 7-10 | intense pain         |

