## 12.4 Other variables

Demographic data (age, gender, weight, body mass index (BMI))

Surgery related data (duration of surgery and anesthesia, precise classification of surgical procedure)

Concomitant medication/therapy on ICU (see NOTE above)

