## \* laboratory measurements in blood/serum sample:

- arterial blood gas analysis/acid base status/electrolytes. Blood sampling for BGA should be performed as close as possible to the time, at which the corresponding hemodynamic measurement is done.
- haemostasis/coagulation parameters (PT, aPTT, Fibrinogen, FVIII:c, vWF-Ag, vWF-RiCo; CT, CFT, MCF using ExTEM und FibTEM)
- cardiac function (Troponin or high-sensitivity Troponin, NT-Pro-BNP)
- inflammatory reaction parameters (facultative: IL-6, IL-10)

**day 0/** intensive care unit (ICU) –

- Aldrete Score (*on admission*)
- Haemodynamics (SAP, DAP, MAP, HR, CVP (on admission and 6hourly); PiCCO: CI, SV, SVR, ITBVI, EVLWI) (on admission and after 6 hours)
- blood gas analysis (arterial or venous blood sample) including acid base status and electrolytes: (on admission, 6 hours after admission). Blood sampling for BGA should be performed as close as possible to the time, at which the corresponding hemodynamic measurement is done.
- abdominal pressure (*6 hours after admission*)
- Ventilatory support as requested to maintain normocapnia and oxygen saturation (PCV, CPAP)
- Concomitant medication, infusion therapy (separate for colloids (i. e. gelatine) crystalloids, blood products)
- Diuresis (sampling period until next morning about 6 o'clock)
- Adverse events and adverse reactions

- check of discharge criteria

**day +1** (1st post-operative day)/ On ICU: Postoperative care will follow a standardised regimen.

- Haemodynamics (SAP, DAP, MAP, HR, CVP(every 6 hours)); PiCCO: CI, SV, SVR, ITBVI, EVLWI (every 12 hours/ in the morning and in the evening)
- abdominal pressure (in the morning)
- Ventilatory support (PCV, CPAP) as requested to maintain normocapnia and oxygen saturation
- Blood sampling for laboratory evaluation\*, urine sample for laboratory evaluation\*\*
- Aldrete Score (in the morning)
- SIRS-criteria
- Nursing Delirium Screening Scale (NuDesc) (three times daily)
- Injury scores (APACHE II, SAPS II, SOFA)
- Assessment of “fit for discharge” criteria (once on ICU - preferably in the morning)
- Concomitant medication including parenteral nutrition, infusion therapy (separate for colloids i. e. gelatine and crystalloid, blood products)
- Diuresis (Sampling period is from morning until next morning about 6 o'clock)
- PONV
- body weight (if possible)

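### Time on ventilator is counted from intubation, so it mixes intraoperative with postoperative ventilation and can mask a difference in the latter (minor, exploratory variable)

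*Protocol*

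**What the plan says.** Protocol section 12.3, under Ventilatory support, defines the variable as "Time on ventilator (measured from intubation in hours". The synopsis uses the same starting point and adds one remark: "measured from intubation in hours; the need of reintubation will be documented". Neither place says when the clock stops or whether ventilation after a reintubation is added.

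Three other places bear on how the variable behaves:

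- Section 12.3, Intraabdominal pressure, places one reading "at the end of surgery (still in operating theatre, directly before extubation". Section 14.1 repeats this for the end of surgery. Extubation in theatre is thus the foreseen course.
- Section 12.3 lists a second ventilation variable directly after the first: "Requirements of postoperative ventilatory support (PCV, CPAP". It has no unit and no start or stop time. Section 14.1 schedules the matching ICU record: "Ventilatory support as requested to maintain normocapnia and oxygen saturation".
- Section 12.4 collects the length of the operation and of the anaesthetic as surgery data: "duration of surgery and anesthesia, precise classification of surgical procedure".

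Section 16.1 plans nonparametric tests for secondary variables. Section 16.2 makes those tests exploratory, without adjustment for multiplicity.

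**The concern.** The protocol's rationale (sections 4 and 5) is that a hyper-oncotic colloid avoids interstitial fluid overload. Longer postoperative ventilation is a plausible clinical expression of such overload, so a ventilation-time variable makes sense.

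A clock that starts at intubation, however, starts before the first bolus of Investigational Product and runs through the operation. A patient extubated in theatre had no postoperative ventilation, yet receives a value of several hours, set by how long surgery took. In a rank test these patients should be tied at the bottom. Instead they are ordered among themselves by operating time. If they are the majority, most of the ranking reflects surgery, and the few patients with prolonged ventilation carry less weight. At stake is the sensitivity of one secondary comparison, for benefit or for harm.

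**Working it through.** **Background figure.** The protocol states no figure for time on ventilator. Its 69 per group, derived for the first primary endpoint (section 16.4: Mann-Whitney, effect size 0.5, two-sided 5%, power 80%), sets the group size used here. Noether's formula reproduces it:

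- p = Φ(0.5/√2) = 0.638
- n = (1.960 + 0.842)² / [6 × (0.638 − 0.5)²] = 68.5 with unrounded p, so 69 per group.

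**Model.** Let A be the time from intubation to end of surgery and V the hours of ventilation after surgery, with V = 0 for extubation in theatre. The protocol's variable is A + V; the alternative is V alone. Power of the two-sided 5% Mann-Whitney test was simulated at 69 per arm for both.

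**Inputs, all assumed.** The protocol gives no share extubated in theatre, no mean or SD of operating or anaesthesia time, and no distribution of ventilation time. Assumed: A normal with mean 6 h and SD 1, 1.5 or 2 h, with the same distribution in both arms; V log-normal with log-SD 0.7 in those ventilated after surgery; 1,500 runs per scenario. Ranges below are across the three SDs.

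| Ventilated after surgery | Median V (h) | Power, V alone | Power, from intubation |
|---|---|---|---|
| 5% vs 20% | 4 | 78-79% | 21-29% |
| 10% vs 30% | 4 | 86-87% | 36-48% |
| 10% vs 30% | 12 | 84-86% | 50-54% |
| 30% vs 50% | 4 | 62-64% | 36-48% |
| 30% vs 50% | 12 | 63-65% | 52% |
| 90% in both arms | 4 vs 6 | 74-76% | 65-72% |
| 90% in both arms | 8 vs 12 | 74-76% | 72-75% |

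**Sensitivity.** With mean A of 7 h, median V of 6 h and SD of A from 0.5 to 2 h, the 5% versus 20% scenario gives 27-35% from intubation and 79-80% from end of surgery. Over both sets of inputs the range from intubation is 21-35%. The loss persists even at an SD of 0.5 h, because small differences in operating time are enough to break the ties among patients extubated in theatre.

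**Does the neighbouring variable compensate?** Suppose the need for postoperative support is analysed as yes/no, at 20% versus 5% with 69 per arm:

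- SE under the null, with pooled proportion 0.125: √(2 × 0.125 × 0.875 / 69) = 0.0563
- SE under the alternative: √[(0.20 × 0.80 + 0.05 × 0.95) / 69] = 0.0548
- power = Φ[(0.15 − 1.96 × 0.0563) / 0.0548] = Φ(0.72), about 77%.

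This is close to the 79% for V alone. When the arms differ in how many patients need support, a yes/no analysis recovers nearly all the lost power. It says nothing about how long support lasted.

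**The case against.** The strongest case against is that the plan does not rest on this variable alone. The need for postoperative support is a separate efficacy variable, the synopsis has the need of reintubation documented, extravascular lung water is measured, and operation and anaesthesia times are collected, so the postoperative part may be separable in the analysis. This stands in part. As shown above, a yes/no analysis of support would detect the differences in proportion for which the loss is worst. It is still not a duration, and the protocol fixes the efficacy variable itself at a starting point that blurs it.

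It is also right that intubation follows randomisation in every arm, so operating time is balanced in expectation. The problem is noise, not bias. Section 16.2 makes the test exploratory, and no power is claimed for it, so no confirmatory conclusion is affected.

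A reader might go further and infer that surgical duration swamps any difference in postoperative ventilation. The documents do not support that. They give none of the rates or SDs needed, and under assumed values the loss runs from large to negligible. Nor does the variable strictly equal anaesthesia time in patients extubated in theatre: intubation to extubation is close to the duration of the anaesthetic, but not identical with it.

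**Conclusion.** The point holds as a minor one. Sections 3 and 12.3 define an exploratory efficacy variable that adds intraoperative to postoperative ventilation, and in the course the protocol foresees it approximates a quantity already recorded in section 12.4.

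The loss of sensitivity is large if postoperative ventilation is uncommon (about 79% down to 21-35% at 20% versus 5%). It is small if ventilation is the rule (about 75% down to 65-75% at 90% in both arms). Every input apart from the group size, the test and the 5% level is assumed. The foreseen extubation in theatre makes the first situation the more natural reading, but the protocol states no rate. It does not follow that a real benefit or harm would go unseen, because the need for support is captured separately.

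**What to change.** In sections 3 and 12.3, define the analysed variable as hours of mechanical ventilation from end of surgery to extubation. This is about 0 for a patient extubated in theatre at the end of surgery, while a delayed extubation in theatre still counts. State whether hours after a reintubation are added. Keep time from intubation as descriptive surgery data.

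The cost is small. The end of surgery and the extubation time are already needed for existing variables, so moving the start is a change of wording. Adding hours after reintubation may need one further CRF time field. A reader might assume those hours are already recorded, but the synopsis says only that "the need of reintubation will be documented".

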#### Nursing Delirium Screening Scale (NuDesc) (see appendix 8)

Lütz A et al. (2008)

includes 5 items, ratings 0 – 2

Measurements will be  
on ICU three times daily

#### Injury scores (see appendix 8)

- SOFA  
Vincent et al., (1996)
- SAPS II  
Le Gall JR et al. (1993)
- APACHE II  
Knaus et al. (1985)

Measurements  
on ICU: once daily

#### Gastrointestinal parameters

- bowel movements on auscultation
- time to full oral nutrition
- time to first defaecation
- time to first flatus

### Intraabdominal pressure

Measurements will be

- baseline (after induction of anaesthesia)
- at the end of surgery (still in operating theatre, directly before extubation)
- 6 hours after end of surgery
- 1st post-operative day in the morning

Technique:

Intraabdominal pressure will be obtained by measuring the intravesical pressure with the patient in a supine position. The bladder will be flushed via the transurethral catheter via a three-way stopcock using 25 mLs of sterile saline. The bladder will be emptied until air reaches three-way stopcock in order to exclude air bubbles in the system and to guarantee patency. As measurement volume 25 mLs sterile saline will be instilled. The manometer/pressure transducer will be connected to the transurethral catheter/connection to bladder via a three-way stopcock. Zero-reference will be at the midaxillary axis (same reference as CVP). Confirmation of correct measurement will be done by control of respiratory variation and the endexpiratory value will be noted.

In the awake patient (measurement at 6 hours after end of surgery and on 1st postoperative day in the morning) pain assessment will be made prior measurement of intraabdominal pressure using visual analogue scale (VAS).

Categories for pain assessment will be

|          |                      |
|----------|----------------------|
| VAS 0    | no pain              |
| VAS 1-3  | mild pain            |
| VAS 4-6  | medium/moderate pain |
| VAS 7-10 | intense pain         |

### Mobilisation

Time until fit for discharge criteria (Marshall S. I., F. Chung (1997, 1999) (appendix 8) are fulfilled.

### Other

Aldrete Score (refer to in Marshall et al. 1999, appendix 8): on admission to ICU and once daily on ICU.

Length of stay in ICU/IMCU (fulfillment of discharge criteria) – assessment will be done once daily (evening) on ICU. If fit-for discharge criteria are not yet fulfilled at POD 5 it will be continued to check until fulfillment or until study end, whatever occurs first.

Morbidity and complication rate: surgical complications such as re-do surgery (e. g. anastomotic insufficiency or bowel leakage), disturbed wound-healing or medical complications which delay time to fully oral nutrition will be assessed and documented at study end

Combined outcome parameter of prolonged length of stay (based on mean length of stay according to the German Diagnosis Related Group System D-DRG) or death.

Health Related Quality of Life (HRQoL) before and 3 months after surgery (EQ-5D, the EuroQol Group, <http://www.euroqol.org>)

**NOTE:** measurements on ICU (if not otherwise mentioned) will be performed until “fit for discharge criteria are fulfilled or until day +5 (incl. day +5) whatever occurs first.

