### **Post-operative patient management**

A standardised therapy management with respect to enteral nutrition, mobilisation etc will be applied and documented in detail in the CRF.

On ICU volume replacement will be performed at the discretion of the attending physician. See “unauthorised concomitant medication”.

For the assessment of the second primary variable, time until fully on oral diet, it has to be assessed for a period of maximally 15 days. It will be assessed for each day (on the subsequent day) whether the patient receives parenteral nutrition. As soon as the patient is off parenteral nutrition and has taken nutrients via oral (not enteral) pathway at least three times that day no further recording of nutritional diet is required.

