## **12 DEFINITION OF THE PRIMARY AND SECONDARY VARIABLES**

### **12.1 Primary Variable**

First primary endpoint: Intraoperatively required amount of HES (mLs) under target controlled volume replacement therapy.

Second primary endpoint: Time until fully on oral (solid) diet (days): Fully on oral (solid) diet is reached when no more parenteral and enteral nutrition is given and the patient has taken nutrients via the oral pathway for at least three times that day.

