## **15 DURATION OF STUDY AND STUDY SCHEDULE**

### **15.1 Duration of study per patient**

Start of study: with randomisation

Treatment period (infusion of Investigational Products):

During surgery (guided by oesophageal Doppler measurements)

End of study: Postoperative day 15 or hospital discharge, whatever occurs first

Last evaluation of certain parameters will be 3 months post-surgery respectively when DRG data are available.

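### The complication rate counts a medical complication only if it delays full oral nutrition, so it omits other medical morbidity and depends on the second primary endpoint

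*Protocol*

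**What the plan says.** The variable is defined twice, in the same way. The synopsis (section 3, efficacy variables) lists surgical complications, with examples, followed by "disturbed wound-healing or medical complications which delay time to fully oral nutrition". Section 12.3, under Other, calls it morbidity and complication rate and repeats the qualifier: "medical complications which delay time to fully oral nutrition will be assessed and documented at study end". No version without the qualifier appears elsewhere in the protocol.

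The outcome inside the qualifier is the second primary endpoint (section 12.1): the day on which no parenteral or enteral nutrition is given and the patient eats at least three times. Under post-operative patient management in section 11, "it has to be assessed for a period of maximally 15 days", and once the criterion is met, "no further recording of nutritional diet is required".

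The complication rate is documented at study end, which section 15.1 defines thus: "End of study: Postoperative day 15 or hospital discharge, whatever occurs first".

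**The concern.** A medical complication enters the rate only through its effect on another trial outcome. Once a patient is fully on oral diet, that date is settled and nothing later can delay it. Take a patient who reaches full diet on day 7 and has a cardiac or renal event on day 9 while still in hospital. That event fails the definition, although the variable is not documented until study end. An earlier medical event also fails if the patient goes on eating.

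Two things are at stake. First, medical morbidity is undercounted in this variable in every arm. Second, whether an event can count depends on a post-randomisation outcome that the trial expects to differ between the HES arms. A lower medical complication rate in the arm that eats sooner could then partly restate the second primary endpoint while looking like separate evidence of less morbidity. Section 6 cites fewer postoperative complications as a benefit of goal-directed fluid therapy, so readers are likely to look at this rate.

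**Working it through.** **Inputs from the protocol (section 16.4).** Assumed difference in time to full oral diet: 1.5 days. Effect size: 0.698. Stated power at 69 per group: 97%. Stated n for 80% power: 37 per group.

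**Reproducing the plan's own figures.** For the Mann-Whitney test, Noether's formula is n = (z₁₋α/₂ + z₁₋β)² / [6(p − 0.5)²], with p = Φ(ES/√2).
- ES 0.698: p = Φ(0.4936) = 0.689. Then n = (1.960 + 0.842)² / [6 × 0.1892²] = 36.5, so 37.
- Power at 69: Φ(√(6 × 69) × 0.1892 − 1.960) = Φ(1.89) = 97.1%.

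Both agree with the protocol. The 1.5-day input is therefore the difference that the plan is built on. The implied standard deviation is 1.5/0.698 = 2.15 days.

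**Inputs that the protocol does not give (assumed).** Mean time to full oral diet in the slower arm, T: 6 to 12 days. Daily hazard of a medical complication, h: 1%, 2% or 4%, constant and equal in both HES arms, so there is no true difference. Every medical complication before full oral diet is treated as countable.

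**Illustration.** Share of patients with a countable medical complication:
- slower arm: 1 − exp(−hT)
- faster arm: 1 − exp(−h(T − 1.5))

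| T slower / faster (days) | h = 1% | h = 2% | h = 4% |
|---|---|---|---|
| 6 / 4.5 | 5.8% vs 4.4%, ratio 0.76 | 11.3% vs 8.6%, ratio 0.76 | 21.3% vs 16.5%, ratio 0.77 |
| 8 / 6.5 | 7.7% vs 6.3%, ratio 0.82 | 14.8% vs 12.2%, ratio 0.82 | 27.4% vs 22.9%, ratio 0.84 |
| 10 / 8.5 | 9.5% vs 8.1%, ratio 0.86 | 18.1% vs 15.6%, ratio 0.86 | 33.0% vs 28.8%, ratio 0.87 |
| 12 / 10.5 | 11.3% vs 10.0%, ratio 0.88 | 21.3% vs 18.9%, ratio 0.89 | 38.1% vs 34.3%, ratio 0.90 |

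Worked cell: 1 − exp(−0.02 × 10) = 18.1%; 1 − exp(−0.02 × 8.5) = 15.6%; 15.6/18.1 = 0.86.

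**Same hazards, one fixed window.** Counting every medical complication to day 15 gives 1 − exp(−0.02 × 15) = 25.9% in both arms, ratio 1.00. In the worked cell, the definition therefore misses 25.9 − 18.1 = 7.8 percentage points in the slower arm and 25.9 − 15.6 = 10.3 in the faster arm.

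**Do other records feed this variable?** No. Section 12.2 lists adverse events as a separate safety item, recorded to postoperative day 5, with later follow-up only of serious events still unresolved then. Section 13.2.1 (recording during the course of the study) and the table in section 14.2 (a mark at three months) suggest a longer period. That is a separate inconsistency, and neither place adds such events to the complication rate.

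**The case against.** A reader might infer that no complication can count after oral diet is reached. The text does not support that. On the natural reading, the qualifier belongs only to medical complications. Re-do surgery, anastomotic or bowel leakage and disturbed wound healing count to study end. The grammar would also allow the clause to govern the whole list, which would widen the problem, but this is the less natural reading.

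A reader might also infer that the trial fails to record medical morbidity. It does not. Creatinine on days 3 and 7, troponin and NT-Pro-BNP to day 1, daily organ-failure and severity scores on ICU, ventilatory support, and the combined outcome of prolonged stay or death all lack the diet condition. The undercount concerns one variable.

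The size is open to challenge, rightly. Only the 1.5 days comes from the protocol. With diet on day 7, 8 of 15 days (53%) could not yield a countable medical event, but only if the patient stays to day 15. With discharge on day 10, it is 3 of 10. The ratios in the table treat all pre-diet events as countable, although some would not delay eating, and they ignore that an event that does delay eating lengthens its own window.

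Finally, one may defend a variable restricted to complications that explain late oral diet, and judging delay is clinical attribution of a familiar kind. That would be reasonable for a variable labelled as such. It does not suit one called morbidity and complication rate.

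**Conclusion.** The point holds for the medical part of the variable. As defined in the synopsis and section 12.3, that part leaves out medical complications that start after full oral diet or do not affect eating. This follows from the wording and needs no assumption about rates. The difference between arms is conditional: it arises only if time to full oral diet differs, as section 16.4 assumes. Under the assumptions shown, the ratio is about 0.76 to 0.90 with equal true morbidity. This is an illustration, not an estimate for this trial.

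Severity is modest. Section 16.2 treats tests of secondary variables as exploratory, and no success or stopping rule uses this one. The trial's primary conclusions are not affected.

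**What to change.** In the synopsis and section 12.3, delete the clause that ties medical complications to delayed oral nutrition. Count all medical complications alongside the surgical and wound complications, and record for each whether it delayed oral nutrition (yes/no) as a descriptive attribute. The events that explain a late diet date can then still be reported as a subset.

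Deleting the clause does not by itself equalise the windows, because study end is day 15 or discharge, whichever is first, so an arm discharged sooner would still be observed for less time. Choose one of two options:
- name one closing day for everyone, such as postoperative day 15, and ask about events after discharge at the three-month call already planned for quality of life; or
- report the rate as in-hospital complications to study end, and state that follow-up length differs between patients.

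The cost is a wording change and a slightly longer case report form entry. The first option also brings some recall-based data for patients discharged before the closing day. Neither option needs an extra visit or test.
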